## Methods

### Study design

This prospective, international, multisite cohort Zika in Infants and Pregnancy (ZIP) study will recruit up to 10,000 pregnant women from ZIKV-endemic regions and follow them longitudinally throughout pregnancy, delivery, and 6 weeks postpartum. Putative cases of ZIKV infection among pregnant women will be identified by monitoring for symptoms of ZIKV-like illness and performing serial laboratory sampling for diagnosis of seroconversion and viral shedding. Infants born to women enrolled in the study will be followed through 1 year of age and evaluated for neurological, audiological, ophthalmological, and other clinical outcomes.

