#### Sample size calculations for primary objectives

The power of the study to detect a difference was estimated by simulation, using the prevalence of ZIKV infection and adverse fetal outcome (Table 3 and Table 4). These power simulations are based on Fisher’s Exact Tests comparing the rate of adverse outcome among ZIKV infected and uninfected participants, and do not adjust for maternal covariates or differences in prevalence or outcomes among different sites or different countries, as the final analysis will do. All simulations were based on 10,000 repetitions and a two-sided unadjusted alpha level of 0.05.

**Table 3 Tab3:** Sample size to detect prevalence of primary outcomes among ZIKV infected and uninfected study participants

Proportion of pregnant women with ZIKV infection	Prevalence of congenital malformations and adverse fetal outcomes among ZIKV uninfected women	Prevalence of congenital malformations and adverse fetal outcomes among ZIKV infected women	Total number of women	Power
15%	1%	2%	6000	65%
			8000	77%
			10,000	85%
		3%	6000	98%
	2%	4%	6000	91%
20%	1%	2%	6000	74%
			8000	84%
			10,000	91%
25%			6000	80%
			8000	90%
			10,000	95%
	2%	4%	6000	97%

**Table 4 Tab4:** Sample size to detect prevalence of primary outcomes among ZIKV infected symptomatic and asymptomatic participants

Proportion of women with ZIKV symptoms	Prevalence of congenital malformations and adverse fetal outcomes among uninfected and asymptomatic women	Prevalence of congenital malformations and adverse fetal outcomes among ZIKV symptomatic women	Total number of women	Power
3%	1%	3%	6000	57%
			8000	69%
			10,000	77%
4%			6000	68%
			8000	78%
			10,000	85%
5%			6000	75%
			8000	84%
			10,000	91%
		4%	6000	94%
			8000	97%
			10,000	99%

Table 3 shows the sample size needed to detect a difference in the prevalence of ZIKV exposure in fetuses and infants of women who become infected with ZIKV compared to women who do not with 90% power, under a range of assumptions. For example, with a 25% prevalence rate of ZIKV infection among pregnant women, a 1% rate of the composite fetal outcome among uninfected women and a 2% rate of this outcome among women with ZIKV infection, we would need at least 8000 women to have 90% power to detect a difference. Assuming a 25% lost to follow-up rate in our sample, this suggests enrolling at least 10,000 women.

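### The 25% loss allowance takes 8,000 women to 10,000 when it should take them to 10,667; at 10,000 enrolled the worked example has about 88% power, not 90%

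*Protocol article*

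**What the plan says.** Under 'Sample size calculations for primary objectives', power is simulated with Fisher's exact test, "comparing the rate of adverse outcome among ZIKV infected and uninfected participants". The settings are given as: "All simulations were based on 10,000 repetitions and a two-sided unadjusted alpha level of 0.05".

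The worked example takes one line of Table 3, in which a quarter of the women are infected and the composite outcome occurs in 1% of the uninfected and 2% of the infected. From this it concludes that "we would need at least 8000 women to have 90% power to detect a difference". The next sentence adds the loss allowance: "Assuming a 25% lost to follow-up rate in our sample, this suggests enrolling at least 10,000 women".

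The figure of 10,000 recurs elsewhere. 'Study design' says that the study "will recruit up to 10,000 pregnant women from ZIKV-endemic regions". 'Sample size considerations' treats 10,000 as the recruitment target, and says a change of sample size, including an increase, will be considered if enrolment or infection rates depart from projection.

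Tables 3 and 4 are both indexed by the total number of women. Table 4 serves the second primary objective (symptomatic infection versus none), and the text applies no loss allowance to it.

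**The concern.** The two consecutive sentences do not fit together. The first makes 8,000 a minimum for 90% power. The second assumes that a quarter of the sample is lost and settles on 10,000. A quarter of 10,000 is 2,500, which leaves 7,500, below the minimum just stated.

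This is the only derivation the article gives for its enrolment figure, and it concerns a primary objective. If the step is wrong, the study meets all its own projections and still falls short of the power it quotes.

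**Working it through.** **Inputs**, all from 'Sample size calculations for primary objectives': two-sided Fisher's exact test, alpha 0.05, no covariate adjustment; 25% infected; outcome rate 1% in uninfected and 2% in infected women; 8,000 women for 90% power; 25% loss; 10,000 enrolled.

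**Step 1. Reproduce the stated power.** Two-sided Fisher power was computed by exact enumeration over binomial outcomes with a fixed 25:75 split.

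| Women analysed | Enumerated | Table 3 |
|---|---|---|
| 6,000 | 79.6% | 80% |
| 8,000 (2,000 vs 6,000) | 89.7% | 90% |
| 10,000 | 94.9% | 95% |

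Table 3 is therefore sound for the number analysed, and the problem is confined to the loss step.

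**Step 2. Check the loss step.** If a fraction d of those enrolled is lost, N enrolled leaves N × (1 − d), so the enrolment needed to keep n evaluable is n/(1 − d).

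- Required enrolment: 8,000/(1 − 0.25) = 10,667.
- Stated enrolment: 10,000, which equals 8,000 × (1 + 0.25). The article does not write the operation out; the exact match is the reason for reading it this way.
- Gap: 10,667 − 10,000 = 667 women, and 667/10,667 = 6.3%.
- Loss that 10,000 does cover: 1 − 8,000/10,000 = 20%.

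**Step 3. Power that 10,000 enrolled delivers at 25% loss.**

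- Evaluable: 10,000 × 0.75 = 7,500, that is 1,875 infected and 5,625 uninfected.
- Exact Fisher power: 87.7% (normal approximation: 88.5%).
- Difference from 8,000: 89.7 − 87.7 = 2.0 points.

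**Step 4. Table 4 at the same 7,500** (outcome 3% in symptomatic women, 1% in the rest).

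| Share symptomatic | Groups at 7,500 | Power at 7,500 | Printed 8,000 row | Difference |
|---|---|---|---|---|
| 5% | 375 vs 7,125 | 81.9% | 84% | 2.1 points |
| 4% | 300 vs 7,200 | 76.3% | 78% | 1.7 points |
| 3% | 225 vs 7,275 | 66.6% | 69% | 2.4 points |

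The comparison is with the 8,000 rows because 8,000 is the number that the worked example intends to have left after loss.

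**The case against.** **The effect is small.** This stands. It is about 2 points in one illustrative scenario. Table 3 itself runs from 65% to 98% over the assumptions considered, and the article says that its simulations ignore covariates and site differences. No endpoint, test or conclusion depends on the slip.

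**Lost women may still contribute.** Fetal demise, neonatal death and malformations seen at birth are known well before the 12-month infant visit, so a late loss may leave part of the composite observed. This stands as a condition on the 87.7%. Of the 2,500 women lost, 500 (20%) would have to remain usable to bring the total back to 8,000. It does not rescue the text, because an allowance for loss already treats the lost as not analysed. The adjustment for loss promised under 'Analyses' addresses bias and does not restore observations.

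**Ten thousand is worded as a minimum.** The minimum itself is what is too low, so this does not help.

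**A reader might infer that the shortfall cannot be recruited**, since 'Study design' gives 10,000 as an upper limit. The document does not support that. 'Sample size considerations' calls 10,000 a target and allows an increase to be considered. The triggers named there are enrolment and infection rates, not loss, but the figure is not a fixed ceiling.

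**A reader might also infer that Table 4 overstates power by 9 or 10 points**, by setting its 10,000 rows (91%, 85%, 77%) against 7,500 evaluable. That corrects a claim the article does not make. No Table 4 row is singled out as the study's power. In Table 3, built the same way, the text quotes the 8,000 row as the number needed before the loss allowance is added. Read consistently, the gap in Table 4 is about 2 points.

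**Conclusion.** The point holds as a minor arithmetic error. An enrolment of 10,000 does not follow from 8,000 evaluable women and a 25% loss; 10,667 does. At 10,000 enrolled and 25% lost, the worked example has about 88% power instead of 90%.

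This rests on three readings: the 25% applies to enrolled women, as the sentence says; lost women give no outcome; and loss is unrelated to infection, so that the 25:75 split is kept. The power values printed in Tables 3 and 4 are not in dispute. What is unclear is only whether their sample size column counts women enrolled or women analysed.

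**What to change.** Replace the loss sentence with one of two statements:

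- 10,000 enrolled with 25% loss gives about 7,500 evaluable women and about 88% power in the worked example; or
- 90% power with 10,000 enrolled holds only if loss is at most 20%.

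State that these figures assume lost women contribute no outcome and that loss is unrelated to infection.

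Label the sample size column of Tables 3 and 4 as evaluable women and add a 7,500 row for the main scenarios. In Table 3, 25% infected and 1% versus 2% gives about 88%. In Table 4, 3% versus 1% gives about 82%, 76% and 67% at 5%, 4% and 3% symptomatic.

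The cost is one sentence, one column label and a few table rows. No extra enrolment or design change is needed; the quoted power becomes slightly less favourable.

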### Study population

ZIP will recruit pregnant women within the first or early second trimester (up to and including 17 weeks and 6 days), age 15 years and older (with assent and consent as required per local country regulations). Additionally, any pregnant women, regardless of gestational age, with acute Zika-like symptoms confirmed by serology and/or RT-PCR are eligible. Recruitment will occur at hospitals and health clinics across Brazil, Colombia, Guatemala, Nicaragua, Puerto Rico, and Peru. At each of these sites, participants may be referred to this study from surrounding clinical centers. Any pregnant women enrolled in other clinical research (including other Zika studies) requiring blood sampling that, in combination with ZIP requirements, exceeds 50 cc every 8 weeks will not be included in ZIP. Women who indicate at screening that they cannot adhere to the proposed visit schedule are also excluded from the study. Infants are eligible for enrollment if they were born to women enrolled in ZIP and have parental consent.

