Pregnancy questionnaire	Monthly visits	Signs/ symptoms of pregnancy complications, including decrease in fetal movement, rupture of membranes, vaginal bleeding, headaches, scotomata, nausea, and vomiting.
Imaging assessments	Once per trimester	Ultrasound results
Environmental/ occupational exposure survey	Once per trimester	Participant’s and her domestic partner’s occupational history; household characteristics; behavioral risk factors (e.g. drinking, smoking); exposure to animals in the home; and exposure to known environmental chemicals
Delivery (live birth or fetal loss) information	At delivery	Mode, location, and outcome of the delivery
Infant Data		
Physical examination and growth parameters	All visits	Examination of cardiac, respiratory, and other systems, and skin and gastrointestinal conditions; weight, length or height, and head circumference; gestational age at birth and Apgar scores (birth visit only)
Hearing, ophthalmologic, and neurological assessments	All visits	General motor development markers, including lethargy, seizures, reflexes, etc.; hearing assessments (otoacoustic emission or automated auditory brainstem response); general eye exams; and ophthalmologic exams to detect chorioretinitis or abnormalities in conjunctiva, lens, or retina. If initial exams are abnormal, infants will be referred for additional audiology and/or ophthalmology testing, and results (if available) from any tests done for clinical reasons will be recorded.
Imaging studies	As done per local standard of care	Any imaging assessments done for clinical care, including any neuroimaging studies (ultrasound, CT, or MRI) obtained for clinical reasons to detect neurologic abnormalities such as intracranial calcifications.
Neurodevelopmental assessment	3, 6, and 12- month visits	Screening neurodevelopmental assessments (Ages and Stages Questionnaire or the Bayley Infant Neurodevelopmental Screener) of all study participants. If results of screening assessment are abnormal, the infant will be referred for diagnostic neurodevelopmental testing using the Bayley Scales of Infant and Toddler Development (BSID) -III.

**Table 2 Tab2:** Specimen collection schedules

Maternal specimen collection schedule							
		First trimester < 14 weeks	Second Trimester < 28 weeks gestation	Third Trimester 28 weeks and greater	Delivery: live birth or fetal loss	6 weeks postpartum +/− 14 days	Zika symptomatic visits
	Screening & Entry	Monthly visits	Monthly visits	Monthly visits			

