Table 4 shows the power of the study to detect a difference in the incidence of congenital malformations and adverse fetal outcomes in fetuses and infants of women who become symptomatic with ZIKV infection compared to women who do not, under a range of assumptions.

A key secondary objective is the association between gestational age at time of ZIKV infection and risk of adverse fetal outcome. With 10,000 women enrolled, if we assume that ZIKV exposure will be approximately uniformly distributed across trimesters and 25% of women become ZIKV positive, we would expect 800–900 women to be infected during their first trimester. If the rate of the composite endpoint among these first-trimester infections was 3%, compared to 1% in those without ZIKV infection, we would have high (> 95%) power to detect a difference. We would also have reasonable power to detect a difference between these first trimester infections and a similar number of infections at later trimesters if the increased risk is limited to the first trimester, if the trimester of ZIKV infection can be confirmed in a large enough group of ZIKV-infected women.

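### The 800–900 first-trimester infections and the power above 95% apply no loss to follow-up and credit every enrolled woman with a fully captured first trimester, which the 25% loss and entry up to 17w6d do not allow

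*Protocol article*

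**What the plan says.** The trimester calculation is in the protocol article, under Sample size calculations for primary objectives. It starts "With 10,000 women enrolled, if we assume that ZIKV exposure will be approximately uniformly distributed across trimesters", takes it that "25% of women become ZIKV positive", and concludes that "we would expect 800–900 women to be infected during their first trimester". The power claim follows: "If the rate of the composite endpoint among these first-trimester infections was 3%, compared to 1% in those without ZIKV infection", power is put above 95%. The article then claims reasonable power for first-trimester infections against a similar number of later ones, provided trimester can be confirmed in enough infected women. That proviso belongs to this last comparison only.

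Three other statements bear on the calculation:
- Earlier in the same section, the step from 8,000 to 10,000 women is justified by "Assuming a 25% lost to follow-up rate in our sample".
- Study population recruits women "within the first or early second trimester (up to and including 17 weeks and 6 days". It also admits women with confirmed acute symptomatic infection at any gestational age.
- Table 2, under Study procedures, heads its first column of monthly visits "First trimester < 14 weeks".

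**The concern.** The assumption that exposure is "approximately uniformly distributed across trimesters" describes when infections happen. It does not say which of them this cohort can see. A woman who enters between 14w0d and 17w6d has her whole first trimester behind her at her first study sample, and any woman who enters earlier has part of it behind her. One third of all infections can be counted as first-trimester only if those acquired before entry are also detected and placed in the right trimester. The figure also uses the 10,000 women enrolled, although the section has just explained that 10,000 is the number inflated for loss.

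The Background names risk by trimester of infection as something earlier studies could not determine, and the article calls this analysis a key secondary one. Under Sample size considerations, the sample size may be cut or expanded if enrolment or infection rates differ from projection. An optimistic projection for this question could therefore feed into that decision.

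**Working it through.** **Inputs from the article.** 10,000 enrolled; 25% infected; one third in each trimester; outcome 3% against 1%; Fisher's exact test, two-sided alpha 0.05, no covariates; 25% loss; entry up to 17w6d; first trimester below 14 weeks.

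**Inputs that are assumptions.** Gestational age at entry, and how far back an entry sample can detect and date an infection. The article gives neither, so ranges are shown.

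**Check of the method.** Exact Fisher power by enumeration matches Table 3. For 25% infected and 1% against 2%, it gives 89.7% at 8,000 women (stated 90%) and 94.9% at 10,000 (stated 95%).

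**Step 1: the article's own figures.** 10,000 × 0.25 / 3 = 833, with 10,000 × 0.75 = 7,500 uninfected. Power is 97.8%, 98.2% and 98.7% for 800, 833 and 900 infections against 7,500. Both stated figures reproduce, with no loss and a full one-third share.

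**Step 2: loss only.**
- 25% of 10,000 lost leaves 7,500 women: 7,500 × 0.25 / 3 = 625 infections against 7,500 × 0.75 = 5,625 uninfected, power 94.3%.
- On the article's own 8,000 evaluable women: 8,000 × 0.25 / 3 = 667 against 6,000, power 95.5%.

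**Step 3: loss and late entry, counting only infections after entry.** Assume a constant weekly risk from entry to week 40, with 25% of women infected in that time. The first-trimester share for entry at week e is (14 − e)/(40 − e), and zero from week 14 on. The count is 2,500 × share × 0.75, compared with 5,625 uninfected.

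| Entry pattern | Share | Count | Power |
|---|---|---|---|
| All at week 6 | 8/34 = 23.5% | 441 | 87% |
| All at week 8 | 6/32 = 18.8% | 352 | 79% |
| Uniform, weeks 6–18 | 32/336 = 9.5% | 179 | 58% |
| All at week 12 | 2/28 = 7.1% | 134 | 47% |

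For uniform entry, 32 is the integral of (14 − e) over weeks 6 to 14, and 336 that of (40 − e) over weeks 6 to 18.

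**Step 4: credit for infections dated from the entry sample.** This is a different model. Start from the 625 of step 2, assume entry uniform from week 8 to 17w6d, and multiply by the average fraction of the first 14 weeks that falls after (entry − look-back).

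| Assumed look-back | Fraction | Count | Power |
|---|---|---|---|
| None | 0.130 | 82 | 32% |
| 4 weeks | 0.362 | 226 | 66% |
| 8 weeks | 0.648 | 405 | 84% |
| 12 weeks | 0.876 | 547 | 92% |

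**Step 5: first trimester against an equal number of later infections, 3% against 1%.** Power is 80% at 833 per group, 67% at 625 and 49% at 441.

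**The case against.** The strongest reply is that the calculation is openly conditional and illustrative, that it concerns a secondary objective, and that loss barely touches its power. Much of this stands. On the article's 8,000 evaluable women, power is still 95.5%, and only the count leaves its range. The 10,000 target rests on Table 3, not on this paragraph, so no primary test or sample size changes.

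The post-entry counts in step 3 also lean low. A positive serology on a routine sample leads to an RNA assay, symptom history is taken at every visit, and women with confirmed acute symptoms can enter at any gestational age, including the first trimester. Some infections present at entry can therefore be dated. A reader might infer that an infection positive at entry can never be placed within pregnancy; the documents do not support that.

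On the comparison between trimesters, 80% at 833 per group is delivered on the article's own inputs. The equal-group figures are also harsher than an analysis that uses every later infection. In the step 3 model, 1,875 infections remain after loss, so the later groups are 1,875 − 441 = 1,434, 1,875 − 352 = 1,523 and 1,875 − 179 = 1,696. Power is then 79%, 73% and 53%. The article itself, however, frames the comparison as one between similar numbers.

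What does not stand is the appeal to the stated conditions. Uniform exposure says nothing about capture before entry, and the proviso on confirming trimester is not attached to the 800–900 or to the power above 95%.

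**Conclusion.** The point holds. The count and the power are correct only with no loss and with complete detection and dating of first-trimester infections. The article's own loss rate and entry window contradict the first condition and make the second untenable without a stated argument.

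The two causes differ in weight. Loss alone moves the count from 833 to 625 (or 667) and leaves power at the borderline, 94.3% to 95.5%. The entry window is the material part. In the scenarios that combine it with loss, power for 3% against 1% falls below 95% every time, but its value depends on assumptions: 47% to 87% counting only infections after entry, and up to 92% with a 12-week look-back.

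A reader might conclude that the count is overstated several-fold. The documents do not establish that. The ratio is 833/547 = 1.5 with the 12-week look-back, 833/441 = 1.9 with entry at week 6, and 833/179 = 4.7 with uniform entry over weeks 6–18. The direction is certain; the size is not, because the article gives neither the distribution of gestational age at entry nor a detection window for IgM. For the same reason, no single replacement range can be read off the article.

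**What to change.** Restate the expected number of first-trimester infections as those that are evaluable and datable, after 25% loss. Declare the assumed gestational age at entry and the assumed means of detecting and dating infections acquired before entry. Show the result as a range, with matching power for both comparisons: first-trimester infection against no infection, and first-trimester against later infection. Extend the caveat on confirming trimester to the claim of power above 95%.

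This needs a recomputed figure and some wording, and no new data. The only cost is a less favourable stated power. Modelling gestational age at infection as a continuous term is an option for the analysis and is not part of this correction.

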### Analyses

The primary analyses will use an indicator of the primary composite endpoint as the response and an indicator of either ZIKV infection with or without ZIKV symptoms as the predictor of interest. These models will be adjusted for site, maternal age at enrollment, season or month of enrollment, and documented infections with CMV and DENV. Additional covariates may be included but will be pre-specified. Participants that are lost to follow-up, outcomes that are missing because of fetal loss before 20 weeks, and propensity for exposure will be adjusted for appropriately. Sensitivity analyses will include alternate models that examine the assumptions behind the primary analysis. A key secondary analysis is the effect of trimester of infection on probability of outcome. This association will be estimated using a similar model to the primary analysis but with an additional indicator variable for trimester of infection. Another key analysis is the comparison of rates of fetal loss between women who experience ZIKV infection with symptoms and those who do not. This will also be fit using similar models to the primary analysis, accounting for loss to follow-up and probability of exposure before 20 weeks. Additional analyses will be carried out to compare the rates in secondary/exploratory outcomes between those ZIKV-infected versus uninfected mothers or between those with and without ZIKV symptoms.

